## Data analysis

Intention-to-treat (ITT) analysis will be performed. The ITT analysis will include all randomized patients in the groups to which they were randomly assigned. Analysis will take into account noncompliance, protocol deviations, dropouts, and anything else that happens after randomization. The two randomized groups will be compared in the treatment period; posttreatment; and at 3 and 6 months after treatment finalization. In addition, within-subject comparisons will be analyzed, contrasting pretreatment and posttreatment scores. The within-group and between-group differences will be examined using mixed-effect models, since these are considered more accurate than univariate and multivariate repeated measures of variance. Group differences will be analyzed after controlling for baseline levels, gender, age, and treatment center. Analysis will be carried out using SPSS version 21.0 (IBM Corp).

For primary outcomes, will consider group differences in anxiety (GAD-7), depression (PHQ-9), and somatic symptoms (PHQ-15) comparing baseline and post-treatment scores using a mixed-effect model. For secondary outcomes, will check between-group differences in the level of disability on daily life domains (work, social, and family life) and quality of life domains (physical, psychological, social, and environmental). The effect sizes of the treatment on primary and secondary outcomes (mean scores) will calculate by applying Morris’s d statistic, where the standardized effect of the treatment is defined as the difference between groups in mean PPC values, divided by the common standard deviation. In addition, a per-protocol (PP) analysis for primary and secondary outcomes will performer only in the patients who completed all follow-up measurements.

Finally, will calculate additional analyses: recovery, reliable recovery, and deterioration rates. The recovery index was defined as pre- treatment scores above the threshold on any of the three scales and below the threshold on all scales at either the post-treatment or 6-month follow-up assessment. The reliable recovery rate will calculate using a change score based on the standard deviation (S.D.). Thus, will use a change score of ≥5 for the GAD-7 and ≥6 for the PHQ-9 and the PHQ-15.

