## Methods

### Study space

This is a multi-center trial carried out in 6 PHC centers; in most of these centers, psychological service is either non-existent or severely limited.

In order to improve mental health services in the country, the study protocol will initially be implemented in the following PHC centers in Santiago de los Caballeros, Dominican Republic: [name] Primary Health Center, El Guano Primary Health Center, Mamachen Primary Health Center, Barrio Obrero Community Center, Hato Mayor UNAP Center and Gurabo Diagnostic Center.

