## Interventions

### Control group treatment

The control group will receive the TAU provided by the primary care physician at the PC center. This treatment has been described in previous research as no treatment, standard treatment, pharmacological treatment and/or practical advice by the GP provided in routine care (Watts et al., 2015). In the Dominican Republic, as in other countries such as Spain (Cano-Vindel et al., 2016), psychotropic drugs are typically given to these patients to lessen the symptoms of the disorders, such as anti-anxiety medications and sleeping pills.

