### Experimental group treatment

The experimental group receive evidence-based group cognitive-behavioral treatment. The protocol that will be applied is based on the protocol originally designed by the PsicAP group in Spain, led by [name]. The protocol is based on 7 sessions, with each lasting 90 min. It will be offered once per week in groups of up to 8 people. The sessions are made up of the following elements:

Psychoeducation that focuses on providing guidance about what emotions actually are as well as their purpose, on the difference between normality and disorders surrounding emotions, and other useful information to counteract some of the misconceptions that the population tends to have about emotions and EDs.Relaxation techniques focused on reducing the physical sensations of discomfort that can trigger ED, including abdominal breathing and progressive muscle relaxation.Training in cognitive restructuring to ensure that patients can identify cognitive distortions and pathological or irrational thoughts that they experience in everyday situations so they can replace them with more logical and healthy alternatives, thus making a change to the emotional intensity associated with distortions and thinking errors.Behavioral therapy, so that patients can identify their emotions and any flawed strategies they may have for regulating emotions and dysfunctional behaviors, replacing them with more functional strategies and repeating them until the individuals develop healthier and more adaptive habits to replace the old patterns.Relapse prevention, to maintain long-term change and ensure that participants can identify their risk situations and the alternatives they have for dealing with them. This includes practicing problem analysis skills from a cognitive-emotional perspective, Use the tools and practical exercises that have helped us. Continuing to practice, until it is overcome. Receiving an additional psychological appointment.

Table 1 outlines the resources used for each component.

**Table 1 Tab1:** PsicAP Protocol components and resources

Therapeutic components	Resources
Psychoeducation	Information about emotions, anxiety, emotional disorders, cognitive-behavioral treatment components, cognitive errors, the relationship between thought and emotion, clarifications about existing misinformation surrounding emotions and emotional disorders.

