## Therapist training

Each PsicAP group is led by a therapist who is also working together with a co-therapist. All of the therapists who are assisting the patients in the Dominican Republic PsicAP project originally graduated with a Bachelor’s degree in psychology, which requires approximately 4 years of university training. One of the basic requirements for taking on a therapist role was also to have a master’s degree in clinical psychology or a related area. Some of the therapists also have a Ph.D. in psychology. Co-therapists have a degree in psychology but have not yet completed a master’s program. The latter received specialized training so they could carry out the initial and final project assessments and assist the therapists appropriately during the sessions.

In order to standardize the therapeutic model to be followed, two significant types of training were done: (1) each therapist had to take an online course on the in TEA platform, which consisted of 45 h of training to refresh themselves on how to manage anxiety disorders (course name: “Refresher on the treatment of anxiety disorders: a cognitive-emotional and transdiagnostic approach” [*“Actualización en el tratamiento de los trastornos de ansiedad: un enfoque cognitivo-emocional y transdiagnóstico”*]); (2) therapists and co-therapists met once a week for seven weeks in order to share the slides and resources from each of the sessions that would be given to the participants, in an effort to establish guidelines so that the therapy in each of the centers would be as homogeneous as possible.

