## Patient recruitment

The study will remain open from the beginning of the assessment until the necessary sample is completed.

The data collection process will be completed once it reaches 300 participants. Sample sizeG*Power3 program were used to determine sample size, which prioritizes statistical power. The effect size measures obtained in the Spanish PsicAP clinical trial were taken into consideration, which were moderate to strong. Based on these analyses, the sample size established for this study was 150 participants per study group (n = 300).

It should be noted that participants will only be included in the study after they have given their informed consent. Patients who do not meet the study inclusion criteria will be referred back to their PHC physician for alternative treatments.

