## Randomization

The simple randomization method is used in this study to assign participants to one of the treatment groups (experimental or control). This kind of randomization is done using the Excel computer program in a 1:1 scheme, which makes it possible to obtain two homogeneous groups.

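### The stated analysis model has no term for the therapy groups in which PsicAP is delivered, so followed as written it understates the standard error of the treatment effect

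*Protocol article*

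**What the plan says.** **Delivery.** On the PsicAP sessions, the Experimental group treatment section says: "It will be offered once per week in groups of up to 8 people". Therapist training adds: "Each PsicAP group is led by a therapist who is also working together with a co-therapist". For the other arm, Control group treatment says: "The control group will receive the TAU provided by the primary care physician at the PC center". No grouping of controls is described.

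**Allocation and setting.** The Randomization section allocates individual patients: "The simple randomization method is used in this study to assign participants to one of the treatment groups (experimental or control". Study space says: "This is a multi-center trial carried out in 6 PHC centers".

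**Analysis.** The Data analysis section gives the model and the reason for it: "The within-group and between-group differences will be examined using mixed-effect models, since these are considered more accurate than univariate and multivariate repeated measures of variance". It then lists the adjustment variables: "Group differences will be analyzed after controlling for baseline levels, gender, age, and treatment center". Neither sentence mentions therapy group or therapist, and the random effects of the model are not named.

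**Size.** Patient recruitment reports a G*Power calculation and concludes that "the sample size established for this study was 150 participants per study group". It gives no alpha, power, single effect size, dropout allowance, ICC or design effect.

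**The concern.** Patients who attend seven weekly sessions together, with the same leaders and the same fellow members, tend to end up more alike than patients from different groups. Here that correlation arises in one arm only.

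The reason given for the mixed model concerns repeated measurements on one patient. It does not concern correlation between members of one therapy group. The one clustering level among the listed covariates is center, whereas the level that the intervention itself creates is therapy group.

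If that level is left out, the variance of the experimental arm's mean is understated. Confidence intervals are then too narrow and p-values too small for GAD-7, PHQ-9 and PHQ-15 alike. The error makes a false claim of superiority more likely, and the Dissemination plan foresees extending the treatment to all primary care centers once its effectiveness has been examined.

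**Working it through.** **Inputs from the protocol article**
- 150 patients per arm (Patient recruitment).
- Therapy groups of at most 8 in the experimental arm only (Experimental group treatment, Control group treatment).
- 6 centers (Study space).
- Smallest effect cited from the Spanish trial: d = 0.40, somatic symptoms (Background).

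**Assumptions, not in the article**
- ICC within therapy group of 0.02, 0.05 or 0.10.
- Two-sided alpha of 0.05.
- Equal group sizes of 8 (the maximum) or 6, and equal total variance in the two arms.

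**The plan's own figure.** The 150 per arm can be neither reproduced nor refuted, because its inputs are not given. For orientation, n = 2(1.96 + z_power)²/d² with d = 0.40 gives 99 per arm at 80% power, 132 at 90% and 163 at 95%.

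**Step 1: number of groups.** 150/8 = 18.75, so at least 19 groups, or 19/6 ≈ 3.2 per center. With groups of 6 there are 150/6 = 25 groups, or about 4.2 per center.

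**Step 2: variance.** With m patients per group, the variance of the experimental mean is multiplied by DE = 1 + (m − 1) × ICC. The control mean is unaffected. The variance of the difference is therefore multiplied by V = (1 + DE)/2.

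**Step 3: type I error when group is ignored.** The true error is 2 × [1 − Φ(1.96/√V)], and the standard error is understated by 1 − 1/√V.

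Worked case, m = 8 and ICC = 0.05: DE = 1 + 7 × 0.05 = 1.35; V = 2.35/2 = 1.175; √V = 1.084; 1.96/1.084 = 1.808; type I error = 7.1%.

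| m | ICC | DE | V | SE understated by | True type I error |
|---|---|---|---|---|---|
| 6 | 0.02 | 1.10 | 1.050 | 2.4% | 5.6% |
| 6 | 0.05 | 1.25 | 1.125 | 5.7% | 6.5% |
| 6 | 0.10 | 1.50 | 1.250 | 10.6% | 8.0% |
| 8 | 0.02 | 1.14 | 1.070 | 3.3% | 5.8% |
| 8 | 0.05 | 1.35 | 1.175 | 7.8% | 7.1% |
| 8 | 0.10 | 1.70 | 1.350 | 13.9% | 9.2% |

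**Step 4: does the center term absorb it?** A simulation used 40,000 null trials with 19 therapy groups spread over 6 centers. It was analyzed with center as a fixed effect and without therapy group. The rejection rate was 4.8% at ICC 0, 7.2% at ICC 0.05 and 9.4% at ICC 0.10. These agree with the formula (5.0%, 7.1%, 9.2%), so adjusting for center does not remove the inflation.

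**Step 5: power when clustering is allowed for.** Power = Φ(d/√((1 + DE)/150) − 1.96). At d = 0.40 with full follow-up and m = 8, it is 91.8%, 89.2% and 84.6% for ICC 0.02, 0.05 and 0.10. With m = 6 it is 92.2%, 90.4% and 87.3%. With no clustering it would be 93.4%.

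**The case against.** **Silence is not a stated assumption.** The strongest reply is that the article names a mixed model without spelling out its random effects, and that the listed variables are covariates. A separate analysis plan, not shown here, may contain a therapy-group effect. This stands as a limit on confidence, and it means one cannot say that the trial declares its patients independent. It does not dispose of the point. The article gives a specific adjustment set that includes center, and it motivates the mixed model by repeated measures only. An analyst working from that text would fit a model whose standard errors are too small.

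**The size is assumed.** This also stands. At an ICC of 0.02 the inflation is under one percentage point. Eight is a ceiling on group size, which is why results for six are shown beside it. The direction holds for any positive ICC.

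**Stronger readings that the article does not support.** A reader might infer that the sample size treats 300 patients as independent and so overstates power. The article states no power and too few inputs to tell whether an allowance was made, so there is no stated power to overstate or restate.

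A reader might also combine clustering with heavy dropout to bring power below 80%. The dropout rate would be the reader's own assumption. An assumed 30% loss (105 per arm) already lowers power at d = 0.40 from 93.4% to 82.6% with no clustering at all, so most of such a fall would come from attrition.

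Nor does the article say that each therapy group has a therapist pair of its own. Pairs may lead several groups.

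**Conclusion.** The concern holds for the analysis model. The trial is partially nested, the model as described has no therapy-group term, and center does not replace one. For assumed ICCs of 0.02 to 0.10, a nominal 5% test has a true type I error of about 5.6% to 8.0% with groups of six and 5.8% to 9.2% with groups of eight. This applies to each of the three primary outcomes.

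Power is a minor matter: at d = 0.40 with 150 per arm and full follow-up it stays at about 85% to 92% over the same ICCs.

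This should be fixed, with moderate confidence. The conclusion rests on reading the listed terms and the stated rationale as the model to be fitted, and its size rests on an ICC that the article does not give.

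**What to change.** Record a therapy-group identifier for every experimental patient in the trial database. In the Data analysis section, add a sentence such as: *The mixed model will include a random effect for therapy group in the experimental arm only, with each control patient treated as a singleton, residual variances estimated separately by arm, and Satterthwaite degrees of freedom.* The within-patient structure for repeated measurements and the listed covariates stay as they are. The therapy-group effect can be fitted in the SPSS mixed-model procedure as a random coefficient on the arm indicator.

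The cost is one extra variable, one sentence of analysis text and slightly wider confidence intervals. No additional patients are needed, and the treatment itself does not change. The identifier should be captured while the groups are running, because it may be hard to recover later.

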In countries like England and Spain, it has been proposed that psychological therapy be included in PHC services in order to ease the aforementioned impacts and improve the mental health of the population [23]; furthermore, the cognitive-behavioral transdiagnostic protocol known as PsicAP was developed in Spain. A randomized controlled trial with 1,691 patients showed that group-administered transdiagnostic CBT was effective in reducing emotional symptoms [14]. Patients who participated in the PsicAP protocol in the intent-to-treat analyses showed a reduction in their anxiety (d = -0.65), depression (d = -0.58) and somatic symptoms (d = -0.40). These effects were also maintained after 12 months of follow-up.

In light of the favorable results obtained by the PsicAP protocol in Spain, the main purpose of this study is to replicate the same clinical trial in the Dominican Republic. Carrying out the PsicAP clinical trial in the Dominican Republic (ClinicalTrial.gov ID: NCT04642092) is a potentially beneficial alternative for country’s mental health in terms of improving life satisfaction, academic, occupational and social well-being, as well as overall quality of life for affected individuals [16]. In addition to the specific benefits for the patients, this improvement could also lead to positive effects for their families and society as a whole, while making better use of government health service financial and time resources, including those of PHC facilities (24–25).

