### Target population

The total intended sample that will be reached in this project is 300 Dominican adults aged 18 to 79. Adult patients from PHC centers who exhibit emotional symptoms (anxiety, depression or somatization) or probable mild to moderate anxiety (generalized or panic), mood or somatization disorders that have been assessed using the Patient Health Questionnaire (PHQ) are eligible (26–27) Specifically, those who meet the study inclusion criteria for the possible diagnosis of any of these disorders or have exceeded the cut-off score on any of the corresponding sub-scales will be part of the study: General Anxiety Disorder-7 (GAD-7) (generalized anxiety ≥ 10), PHQ-9 (depression ≥ 10), PHQ-15 (somatization ≥ 5), PHQ- Panic Disorder (PHQ-PD) (positive and panic ≥ 8, including the first 4 items). Patients who score ≥ 24 on the PHQ-9 or with suicidal ideation will be excluded and referred to a specialist.

All patients in PHC centers will have the same opportunity to be assessed in order to determine whether they could benefit from PsicAP psychological treatment. Those who meet the study inclusion criteria will be invited to be part of the study and, after accepting and signing the informed consent of their own free will, they will be distributed equally at random (1:1) between the control group (receiving the conventional treatment used in PHC facilities up to this point) and the experimental group (who will receive the PsicAP treatment).

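### Baseline is both a response and a covariate in the primary mixed model, so the group-by-time contrast reduces to an unadjusted change-score comparison

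*Protocol article*

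**What the plan says.** All the relevant text is in the Protocol article, Data analysis.

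- For the three primary scales (GAD-7, PHQ-9, PHQ-15), group differences are to be assessed by "comparing baseline and post-treatment scores using a mixed-effect model".
- One family of models serves both kinds of contrast: "The within-group and between-group differences will be examined using mixed-effect models". The section also announces that "within-subject comparisons will be analyzed, contrasting pretreatment and posttreatment scores".
- On adjustment: "Group differences will be analyzed after controlling for baseline levels, gender, age, and treatment center".
- The effect size is Morris's d, the "difference between groups in mean PPC values, divided by the common standard deviation", which is a contrast of pre-post change.

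No sentence takes baseline out of the responses, constrains the arm means to be equal at baseline, or lets the baseline covariate act differently at different visits.

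**The concern.** Each role for baseline is legitimate alone. As a response, it supports a comparison of change. As a covariate, it supports a comparison of later scores that is more precise than change. Put together in one model, the baseline rows are regressed on themselves. The between-arm contrast of change then gains nothing from the covariate, although the plan appears to promise a baseline-adjusted comparison. Depending on the rows fitted, the reported standard error may also be wrong. At stake is the precision, and possibly the error rate, of the primary test on all three primary scales.

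**Working it through.** **Inputs.** From the documents: 150 per arm ("the sample size established for this study was 150 participants per study group"), and an effect of 0.40 SD, the smallest of the three effects quoted in Background from the Spanish trial (somatic symptoms). Assumed, because the article does not give them: SD 1 at both times, pre-post correlation ρ of 0.3, 0.5 or 0.7, two-sided 5% level, complete data.

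**The plan's own figure.** The sample size is stated without alpha, power or design effect, so 150 per arm cannot be reproduced. As a reference, an unadjusted two-sample comparison with 150 per arm has 93.4% power for 0.40 SD at two-sided 5%.

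**Step 1: what the contrast estimates.** Write the model as score = arm + visit + arm×visit + baseline + gender + age + centre + person intercept + error, with the baseline visit among the rows. Baseline, gender, age and centre are constant within a person, so they cancel from that person's post-minus-baseline difference. The arm×visit coefficient for post-treatment is therefore exactly the difference between arms in mean change.

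**Step 2: its precision.** Variance factors, each multiplied by 2/150 for the contrast between arms:

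- change score: 2(1−ρ)
- baseline-adjusted (ANCOVA): 1−ρ²
- ratio: 2(1−ρ)/(1−ρ²) = 2/(1+ρ)

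| ρ | SE change | SE ANCOVA | Variance ratio | Power for 0.40 SD, change (correct SE) | Power, ANCOVA |
|---|---|---|---|---|---|
| 0.3 | √(1.40×2/150) = 0.137 | √(0.91×2/150) = 0.110 | 1.54 | 82.6% | 95.0% |
| 0.5 | √(1.00×2/150) = 0.115 | √(0.75×2/150) = 0.100 | 1.33 | 93.2% | 97.8% |
| 0.7 | √(0.60×2/150) = 0.089 | √(0.51×2/150) = 0.082 | 1.18 | 99.5% | 99.9% |

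Power is from 4,000 simulated trials per setting. With unequal SDs s₀ and s₁, the change-score variance exceeds the ANCOVA variance by (s₀−ρs₁)², so change is never the more precise of the two.

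**Step 3: two rows per person, random intercept.** The within-person part estimates the residual variance as 1−ρ. The person mean, given baseline, has residual variance (1−ρ²)/4, which the model equates to intercept variance + (1−ρ)/2. Hence intercept variance = (1−ρ²)/4 − (1−ρ)/2 = −(1−ρ)²/4. This is negative for every ρ below 1, so the estimate goes to zero; it did so in every simulated trial. The pooled residual variance becomes (1−ρ)(3+ρ)/4, and the reported SE is the true SE times √((3+ρ)/4).

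| ρ | SE factor | SE too small by | Actual z cut-off | Type I error, closed form | Simulated |
|---|---|---|---|---|---|
| 0.3 | √0.825 = 0.908 | 9% | 1.96×0.908 = 1.780 | 7.5% | 7.4% |
| 0.5 | √0.875 = 0.935 | 6% | 1.96×0.935 = 1.833 | 6.7% | 7.0% |
| 0.7 | √0.925 = 0.962 | 4% | 1.96×0.962 = 1.885 | 5.9% | 5.6% |

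**Step 4: four rows per person** (baseline, post-treatment, 3 and 6 months), compound symmetry. The person mean given baseline has residual variance (9/16)(1−ρ)(1+3ρ)/3, equated to intercept variance + (1−ρ)/4. Hence intercept variance = (1−ρ)(9ρ−1)/16, which is positive once ρ exceeds 1/9 ≈ 0.11. There is then no collapse. In 1,500 simulated trials per setting, type I error was 4.9%, 4.7% and 5.2% at ρ 0.3, 0.5 and 0.7, and the model SE matched the empirical SE (0.137 and 0.138; 0.115 and 0.116; 0.090 and 0.088). The precision loss of Step 2 remains.

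**Step 5: a group main effect over the baseline and post rows.** The baseline row carries no treatment effect, so the coefficient averages 0 and 0.40 to (0+0.40)/2 = 0.20.

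**The case against.** The strongest reply is that the article writes no model equation. It introduces the pre-post contrasts separately from the group comparison, speaks of models in the plural, and ties the baseline adjustment to group differences only. The authors may intend baseline as a response for the within-group contrasts and as a covariate for the between-group test. An article may also leave exact specification to a fuller document. This reading is available, and under it the analysis would be sound. But the sentence on the primary outcomes itself joins group differences to the comparison of baseline with post-treatment scores. The conflict therefore lies in what is stated, not in what is left out.

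Two stronger inferences are tempting, and the text does not support them. A reader might conclude that type I error is necessarily inflated. That needs the two-row random-intercept fit of Step 3; the section also plans comparisons at 3 and 6 months, and with those rows in the model the error rate is nominal. A reader might also conclude that the trial would report about half the true effect. That needs a group main effect across baseline and post rows, which the text never names as the test, and Morris's d as defined is not halved.

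It also stands that a change-score comparison is unbiased under randomization, so the certain loss is one of precision.

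**Conclusion.** The point holds as a stated conflict over baseline's role. In both layouts examined, the group-by-time contrast is the change-score difference and the covariate buys nothing. The variance is 1.54, 1.33 or 1.18 times that of a baseline-adjusted analysis at correlations of 0.3, 0.5 or 0.7. At 0.40 SD the cost in power is about 12 points at 0.3 (82.6% against 95.0%), 5 at 0.5 and under 1 at 0.7.

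The understated SE (about 4–9%) and type I error of roughly 6–7.5% are conditional on fitting only two rows with a random intercept. At ρ = 0.7 the simulated 5.6% is within two Monte Carlo standard errors (0.34% each) of 5%, so the case there rests on the closed form. Dilution by half is conditional on a test the plan does not name.

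The sizes rest on the assumed correlations, equal SDs and complete data. The conclusion that baseline adjustment is never less precise than change does not depend on the correlation or on equal SDs. The matter is moderate in size and worth correcting because it concerns the primary test.

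**What to change.** Use baseline once in the between-arm model, in either of two ways.

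- Take only the post-treatment and follow-up scores as responses, with fixed effects for arm, visit, arm-by-visit, baseline score of the same scale, baseline-by-visit, gender, age and centre.
- Or keep baseline as a response, constrain the arm means to be equal at baseline, and drop the baseline covariate.

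In both, name the arm contrast at post-treatment as the primary estimate. Reword the sentence on the primary outcomes to match, and describe the within-group pre-post contrasts as a separate descriptive analysis. With the first option at 150 per arm, the SE is 0.110, 0.100 or 0.082 at correlations of 0.3, 0.5 or 0.7.

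The cost is wording only; no new data are needed.

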### Hypotheses

The hypotheses derived from the study objectives are that, in post-treatment and continuing through follow-up, patients who participate in the transdiagnostic cognitive-behavioral group treatment (PsicAP), as compared to the control group receiving typical treatment, will experience:

A more noticeable decrease in anxious, depressive and somatic symptoms.Higher rates of remission when screening for possible anxiety, depressive and somatic disorders.Better work, social, and domestic functioning.A better quality of life.A more noticeable decrease in risk factors for cognitive distortions and emotional regulation strategies.

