### Patient health questionnaire-15 (PHQ-15)

The PHQ-15 uses 15 items to ascertain how often participants have been inconvenienced by somatic symptoms in the past four weeks. Each answer option is scored from 0 to 2, with the total thus ranging from 0 to 30. Scores of 5, 10 and 15 are the cut-off points for low, medium or high severity in terms of somatic symptoms, respectively.

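### The recovery index is met at post-treatment or at 6 months, so it cannot show whether remission is maintained; secondarily, the 6-point PHQ-15 change rule cannot be met from the entry score of 5

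*Protocol article*

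**What the plan says.** All references are to the protocol article.

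- **Recovery (Data analysis).** The index requires pre-treatment "scores above the threshold on any of the three scales" and later scores "below the threshold on all scales at either the post-treatment or 6-month follow-up assessment". This is one index covering two visits. No version for each visit is given.
- **Reliable recovery (Data analysis).** "The reliable recovery rate will calculate using a change score based on the standard deviation (S.D", and the plan "will use a change score of ≥5 for the GAD-7 and ≥6 for the PHQ-9 and the PHQ-15". The section does not say whether the change is needed on one scale, on every scale elevated at baseline, or on all three.
- **Entry (Target population).** Patients who "have exceeded the cut-off score on any of the corresponding sub-scales will be part of the study" are eligible. The somatization cut-off is "PHQ-15 (somatization ≥ 5".
- **Scale (PHQ-15 measure).** Each of the 15 items scores 0 to 2, "with the total thus ranging from 0 to 30".
- **A second somatization entry rule (Inclusion criteria).** This asks for at least three symptoms at maximum intensity.
- **What the trial wants to learn.** Main objective lists remission among the main outcomes and asks whether results last to 6 months. Hypotheses predicts higher remission rates "in post-treatment and continuing through follow-up".

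**The concern.** An either/or rule across two visits scores each patient on the better of the two. It counts three groups as recovered: those well at both visits, those well only at 6 months, and those well at post-treatment who have relapsed. The last group is the one a question about maintenance has to separate out. A reader of the results would see one recovery percentage, higher than the rate at either visit or at best equal to it, and could take it as evidence that remission lasts.

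The reliable-change rule has a narrower problem. It sets a 6-point fall on a scale whose entry cut-off is 5 and whose floor is 0. Patients at the bottom of the PHQ-15 entry range therefore cannot satisfy the PHQ-15 criterion, however well they do.

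**Working it through.** **1. What the either/or rule implies by logic alone.** Let A be below threshold on all scales at post-treatment and B the same at 6 months, among the same patients. The index is P(A or B) = P(A) + P(B) − P(A and B). Since P(A and B) cannot exceed P(A) or P(B), the index is at least as large as each of them. If nobody recovers for the first time after treatment ends, B lies inside A and the index equals P(A), whatever share of patients relapses. No assumed figure is needed for this step.

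**2. Illustration of size.** The documents give no recovery rate and no between-visit correlation, so both are assumed. Take recovery p at each visit and phi correlation φ between visits:

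- P(both) = p² + φ·p(1 − p) = 0.16 + 0.5 × 0.24 = 0.28 for p = 0.40, φ = 0.5
- P(either) = 2p − P(both) = 0.80 − 0.28 = 0.52
- Well at post-treatment only = 0.40 − 0.28 = 0.12
- Share of the recovered who are not below threshold at 6 months = 0.12 / 0.52 = 23%

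Extremes for p from 0.30 to 0.50 and φ from 0.3 to 0.7:

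| p | φ | P(both) | P(either) | post only | share |
|---|---|---|---|---|---|
| 0.30 | 0.3 | 0.153 | 0.447 | 0.147 | 33% |
| 0.50 | 0.7 | 0.425 | 0.575 | 0.075 | 13% |

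The result depends on how correlation is expressed. With a bivariate-normal correlation of 0.5 and p = 0.40, the figures are 56% for either, 24% for both, and a share of 29%. Over p from 0.2 to 0.6 and correlation from 0.3 to 0.9, the share runs from 10% to 40%.

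**3. PHQ-15 change rule.** The 6-point figure is said to rest on a standard deviation. It cannot be reproduced, because the article gives no standard deviation, reliability or multiplier. The check is therefore scale arithmetic: the end score must be at most the baseline minus 6, and it cannot be below 0. The recovery threshold is not restated in Data analysis. I assume it equals the entry cut-off, so that below threshold means 4 or less.

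| Baseline | End score needed for a 6-point fall | Attainable? | Fall needed to reach 4 |
|---|---|---|---|
| 5 | −1 | no | 1 |
| 6 | 0 | only at the floor | 2 |
| 7 | 1 | yes | 3 |
| 8 | 2 | yes | 4 |
| 9 | 3 | yes | 5 |
| 10 | 4 | yes | 6 |

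From 10 upward, crossing the cut-off already implies a fall of at least 6. The other two scales do not have this difficulty at their entry cut-offs of 10: GAD-7 needs 10 − 5 = 5 and PHQ-9 needs 10 − 6 = 4, both attainable.

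**4. The competing entry rule.** Three symptoms at 2 points each give a PHQ-15 of at least 3 × 2 = 6. Under that rule nobody enters on somatization at 5, but a patient at 6 would still have to reach 0.

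**The case against.** **The wording may mean a rate at each visit.** The same section compares the groups separately at post-treatment and at follow-up, so the authors may have intended two rates. That is possible, but the sentence defines one index joined by an or. One sentence settles it on either reading.

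**Waning is not invisible.** A reader might infer that the plan conceals relapse altogether. It does not: the mixed models compare symptom scores at each follow-up, so a fading mean effect would show there. The limitation belongs to the recovery index.

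**The index is an additional analysis.** Data analysis lists it after the three symptom scores, which it names as primary, and no section says that this index is how remission will be measured. Likewise, Hypotheses speaks of group differences that continue, and does not define remission as sustained in each patient. Both points stand and limit the weight of the finding. Remission is still listed as a main outcome, and this is the only recovery rule for it in the article.

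**Inflated levels are not a biased comparison.** A reader might infer that the rule favours one arm, because a patient seen twice has two chances. With no treatment effect, 40% recovery per visit, φ = 0.5, complete post-treatment data and 6-month completion of 80% versus 60% (all assumed), with a missed visit counted as not recovered, the rates are 0.40 + 0.12 × 0.8 = 49.6% and 0.40 + 0.12 × 0.6 = 47.2%. That is 2.4 points from a 20-point difference in completion. The section also says the intention-to-treat analysis will take dropouts into account. A material between-arm bias is not shown.

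**Unattainable does not mean forced to fail.** A reader might infer that every patient with a PHQ-15 of 5 is bound to fail reliable recovery. The documents do not support that. No rule for combining scales is given, so a patient also elevated on GAD-7 or PHQ-9 might qualify there. If above the threshold is strict, a score of exactly 5 is outside the index at baseline. The Inclusion criteria imply 6 or more. A reliable-change rule is also meant to exclude small changes, and it applies equally to both arms.

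**Patients who enter on the panic scale alone.** They may seem to be recovery failures by construction. They are not: the baseline condition simply places them outside the index.

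**Conclusion.** The concern holds in limited form. As written, the index counts a patient who has relapsed by 6 months as recovered and can never be lower than the rate at either visit. It therefore cannot show whether remission is maintained. That conclusion follows from the definition. The size does not: 52% reported against 40% at each visit, with 23% of the recovered no longer below threshold at 6 months (13% to 33%), rests wholly on assumed rates and correlations.

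The secondary point also holds narrowly. The PHQ-15 criterion cannot be met from 5 and from 6 requires a score of 0, so a patient elevated only on the PHQ-15 at 5 cannot meet it. How many patients this affects is unknown, and it depends on which somatization entry rule applies and on how the scales combine.

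**What to change.** 1. Replace the either/or rule with three rates: recovery at post-treatment, recovery at 6 months, and sustained recovery, meaning below threshold on all scales at both visits.
2. Use one denominator for all three, namely randomized patients above threshold at baseline, with the same missing-data handling in both arms. If the statistical analysis plan already fixes this, a pointer to it is enough.
3. State the recovery thresholds, including whether a score equal to the cut-off counts as above it.
4. State how the change criteria combine across scales. One option is to require the change on a scale that was elevated at baseline and on which it is attainable. Restricting the PHQ-15 component to baselines of 6 or more removes the impossibility, but a patient at 6 must still reach 0, and this should be acknowledged.
5. Reconcile the somatization entry rules under Target population and Inclusion criteria.

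The change to the recovery rates is analysis wording only and uses assessments already planned, with no new visits or patients. The price is that reported recovery rates will be lower than the pooled index would give, and the sustained rate lowest of all.
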